**Trial registration number:**

DRKS00017654.

STRENGTHS AND LIMITATIONS OF THIS STUDYA comprehensive evaluation will be provided regarding the ability of this new treatment approach in form of relapse prevention to treat back pain adequately and, furthermore, support patients in their behaviour and motivation to take care of their back health themselves before chronicity occurs.The results will contribute a better understanding of whether the acceptance of the programme could be increased by involving and closely accompanying the patients and providing them with concrete training instructions, which highlights high demands on the treatment concept that are not covered by standard outpatient care.The primary outcome is not collected via questionnaires but rather via claims data, so that an information bias can be excluded in this respect.As a cluster-randomised study with monthly randomisation, a certain degree of contamination, due to personnel changes, for example, is unavoidable, which is a limitation of the methodology.As a limitation for the primary outcome, it should be taken into account that the days of incapacity to work are based on incapacity certificates issued by the treating physician, which are usually only submitted to the health insurance funds for incapacity to work lasting 3 days or longer, but since a period of incapacity to work for more than 2 days is usually to be expected in the case of back pain, the impact is likely to be small.

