### Outcome evaluation

The results will be derived from a cluster-randomised controlled trial. The evaluation design incorporates an IG as well as a CG and surveys at three different points in time (see figure 2). Both groups will participate in the MPT programme. While IG members will additionally receive relapse prevention modules, the CG will undergo usual care. The primary outcome represents the number of days of incapacity to work within 1 year after the end of MPT. It is assumed that in the present sample, the average number of 37 days off work per year will decrease in the IG by 40% (or 15 days) compared with the CG. One secondary outcome addresses the functional capacity. It is assumed that the functional capacity in the IG will be significantly (p<0.05) higher than in the CG. In addition, patient and provider satisfaction with the intervention will be explored, including barriers, hurdles and potentials. Direct and indirect costs are another outcome and will be compared between IG and CG.

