### Measurements

Various instruments will be used in the course of primary data collection, including standardised questionnaires (table 1). Prior to the start of MPT, the IG and CG will receive a questionnaire to assess the status quo at the beginning of the intervention (T0). The questionnaire will be handed out directly at the Rehabilitation Center or sent by mail in individual cases for T0 and after the 4-week MPT programme (T1). It will comprise various items on socio-demographic and socioeconomic parameters together with health-related behaviour (exercise, diet, smoking, etc). Health-related questionnaires will be the Heaviness of Smoking Index,^22^ the AUDIT alcohol consumption questionnaire, an effective brief screening test for problem drinking^23^ and the Pain Disability Index.^24^ In addition, the questionnaire will include items about how often and to what extent the study participants exercise,^25^ as well as questions about diet and nutrition.^26^ In addition, standardised survey instruments will be included to assess functional capacity (Questionnaire for the diagnosis of functional disability caused by backache, FFbH-R)^27^ and health-related quality of life (EQ-5D).^28^ A Visual Analogue Scale will be used to assess the patient’s health-related quality of life from 0 to 100. IG and CG will receive further questionnaires 12 months post intervention (T2). All questionnaires except for T0 will include questions regarding patient satisfaction and experience with the intervention. Two weeks after handing out or sending the questionnaire, patients who have not yet responded will receive a reminder to increase the response rate. A second reminder will be sent after an additional 10 days. Reminders and the final questionnaires (T2) for the IG will be sent by the Rehabilitation Center, while those for the CG will be sent by the health insurance fund.

**Table 1 T1:** Quantitative and qualitative data sources

Target group	Data source	Data type	Instrument	Parameter
Patients	Primary data	Quantitative	Questionnaire	Age, gender, sociodemography, satisfaction, functional capacity, health-related quality of life, impairment due to pain, health behaviour, sports activity, nutrition, smoking and alcohol
Medical staff and psychologists	Primary data	Qualitative	Interview	Motivation, expectations, experiences, hurdles and barriers, suggestions for improvement and satisfaction with the intervention

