Patients	Secondary data	Quantitative	Claims data	Days of incapacity to work, region, pharmaceuticals, therapeutic products and outpatient and inpatient care

Secondary data will be included in the analyses based on claims data of the regional health insurance fund AOK Lower Saxony. These will include inpatient treatment, rehabilitation services, pharmaceuticals and remedies along with days of incapacity to work. Moreover, sociodemographic factors of influence (eg, age, gender and level of education) together with data regarding health-related quality of life will be included in the analysis.

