### Study population

The study population will comprise members of the regional health insurance fund AOK Lower Saxony, residing in the northwest of Lower Saxony (see online supplemental figure S1). The specific inclusion and exclusion criteria are shown in table 2.

10.1136/bmjopen-2022-067412.supp1Supplementary data

**Table 2 T2:** Inclusion and exclusion criteria

Inclusion criteria	
Membership	AOK Lower Saxony
Region	Northwest of Lower Saxony (see online supplemental figure S1)
Sick pay	Entitled
Incapacity to work	At least 21 days during the last 6 months
Diagnoses	Back pain (ICD: M40–M54, excluding M45, M46 and M49)
Exclusion criteria	
Age	≥62 years
Diagnoses	Mental and behavioural disorders (ICD: F00–F99; 6 months before) Malignant neoplasms (ICD: C00–C97; 12 months before incapacity to work) Injuries (ICD: S00–S99; 6 months before incapacity to work) Chronic back pain (duration of the incapacity to work within the last 6 months is cumulatively longer than 12 weeks)

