#### Primary outcome

The data will be analysed by reference to the primary outcome (days of incapacity to work), which is carried out by intention-to-treat analysis. Patients are analysed according to their original group assignment.

To test the primary hypothesis H_1_ ‘The intervention reduces the number of days of incapacity to work’, an analysis of covariances with cluster adjustment will be performed, using a significance level of 0.05. Covariables included into the model will be age, gender and comorbidities (eg, depression). In addition, a hypothesis test (two-sided t-test with a significance level of 0.05) will be performed.

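### The primary ANCOVA does not name incapacity days before MPT as a covariate, so the plan gives up some precision, though it introduces no bias

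*Protocol article*

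**What the plan says.** For H1 the article (Primary outcome) plans that "an analysis of covariances with cluster adjustment will be performed, using a significance level of 0.05", and then: "Covariables included into the model will be age, gender and comorbidities (eg, depression". It adds a second test of the same hypothesis, a "two-sided t-test with a significance level of 0.05".

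The outcome is defined under Outcome evaluation: "The primary outcome represents the number of days of incapacity to work within 1 year after the end of MPT". On its source, the strengths and limitations list says: "The primary outcome is not collected via questionnaires but rather via claims data". Of the claims data, Measurements says: "These will include inpatient treatment, rehabilitation services, pharmaceuticals and remedies along with days of incapacity to work".

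Eligibility rests on the same quantity. Table 2 (Study population) requires incapacity to work of "At least 21 days during the last 6 months" and excludes patients whose cumulative incapacity over those 6 months exceeds 12 weeks. Study design says that the rehabilitation centre learns the allocation in the third week of MPT and that neither patients nor staff know it before then.

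For H2 (functional capacity), Secondary outcomes states only a two-sided t-test. The FFbH-R is part of the questionnaire given before MPT "to assess the status quo at the beginning of the intervention (T0"). It is collected again after the 4-week MPT (T1) and 12 months post intervention (T2).

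**The concern.** The earlier value of the outcome is usually among the better predictors of its later value. Here it is recorded in the same source as the outcome, settled before allocation is known, and already used to select patients, yet the named covariates leave it out. Of the covariates that are named, the only comorbidity given as an example, depression, falls under the F00–F99 exclusion for the preceding 6 months (Table 2), so it can be expected to vary little in this sample.

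At stake is the width of the confidence interval for the primary effect. With about 24 monthly clusters and no stratification described, the arms will differ somewhat by chance in prior sick leave. Part of that difference enters the unadjusted estimate as random error, which adjustment would remove. The same reasoning applies to H2 and the T0 FFbH-R.

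**Working it through.** **Inputs from the article (Sample size calculation).** Mean 37 days, SD 58, reduction 40% or 15 days, stated d = 0.3409275, two-sided alpha 5%, power 80%, 137 per group, ICC 0.01, average cluster size 15.3, stated design effect 1.1, 147 per group after clustering.

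**Assumed, because the documents give no figure.** r is the correlation between pre-MPT and follow-up days after the named covariates have been allowed for. Range shown: 0 to 0.5.

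**The plan's own figure.** From d = 0.3409275 the two-sample t-test needs 136.02, rounded up to 137 per group, so 137 reproduces from d. But d does not follow from the stated SD: 15/58 = 0.259, while 15/0.3409275 = 44.0 would be the implied SD. Both values of d are therefore carried below.

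**Design effect.** 1 + (15.3 − 1) × 0.01 = 1.143, not 1.1. Effective number per group: 147/1.143 = 128.6.

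**Effect of adjustment.** Residual variance is multiplied by 1 − r², so the detectable standardised effect becomes d/√(1 − r²). The equivalent gain in patients is 1/(1 − r²). Power is from the noncentral t with 128.6 per group.

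| r | 1 − r² | equivalent patients | power, d = 0.341 | power, d = 0.259 |
|---|---|---|---|---|
| 0 | 1.00 | 1.00 | 78% | 54% |
| 0.2 | 0.96 | 1.04 | 79% | 56% |
| 0.3 | 0.91 | 1.10 | 81% | 58% |
| 0.5 | 0.75 | 1.33 | 88% | 66% |

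The normal approximation runs about 0.3 points higher, which rounds to 82% and 67% in the two cells at 81% and 66%. The table assumes that adjustment leaves the design effect unchanged.

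**In days, with SD 58.** The standard error of the difference is 58 × √(2/128.6) = 7.2 days. Multiplied by √(1 − r²) it becomes 7.1, 6.9 and 6.3 days at r = 0.2, 0.3 and 0.5. If prior days have the same ICC, the component due to chance imbalance in them is r × 58 × √(2/128.6), that is 1.4, 2.2 and 3.6 days, against a target of 15.

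**Could the covariate alone restore 80%?** At 128.6 effective patients per group, 80% power needs a standardised effect of 0.351. With d = 0.259, 1 − (0.259/0.351)² = 0.46, so r of about 0.68 would be required. With d = 0.341, 1 − (0.341/0.351)² is about 0.055, so r of about 0.23 is enough.

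**How large r might be.** Table 2 confines 6-month days to between 21 and 84 (12 weeks × 7). Restricting the range of a predictor generally weakens its correlation with the outcome, so the upper rows of the table are the more plausible ones.

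**The case against.** The strongest reply is that nothing here is invalid. Under randomisation the planned ANCOVA is unbiased without the baseline value, and its standard error already reflects chance imbalance. That stands: a reader might infer bias, or that imbalance passes in full into the estimate, and neither follows. Only the part proportional to the regression slope enters, and on the planning ICC clustering enlarges the standard error by only about 7% (√1.143 = 1.07).

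Second, the covariate list may not be exhaustive. Measurements says that education and quality-of-life data will also be included in the analysis, although neither is named for the primary model, and a separate analysis plan is mentioned but not shown. This is fair. Still, the article does name covariates for its primary model, and no section names prior incapacity days among them.

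Third, data availability. The eligibility rule shows that the insurer holds 6 months of history. It does not show that 12 months, or indeed any pre-MPT period, is in the claims delivery to the evaluator. That stands and shapes the fix.

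Fourth, the table compares with r = 0, whereas age, gender and comorbidities are already in the model. Only the increment counts, which is why r is defined after those covariates.

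Fifth, for H2 the text does not say whether the t-test is on the T2 score or on change from T0. A reader might infer that T0 is ignored. The documents do not establish that, only that a t-test, and not an ANCOVA on T0, is stated.

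**Conclusion.** The point holds as a loss of efficiency in the primary analysis that is cheap to avoid. Its size cannot be taken from the documents. Over r = 0.2 to 0.5 it is 4% to 25% of residual variance, with the lower end plausible given the 21–84 day restriction. In power at 147 per group, this is about 1 to 10 points with the stated d (from 78% to between 79% and 88%) and about 2 to 12 points with d = 0.259 (from 54% to between 56% and 66%). These figures rest on ICC 0.01, design effect 1.143 and the assumed r.

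It is tempting to present the covariate as the remedy for an underpowered trial. The article itself claims 80% power. The low 54% comes from the conflict between SD 58 and the stated d, which has to be reconciled separately and which adjustment would cure only at an r near 0.68. The benefit of adding MPT track (standard or complex) cannot be quantified from the documents.

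**What to change.** - **H1:** prespecify pre-MPT incapacity days from claims as a covariate in the cluster-adjusted ANCOVA, over a fixed look-back ending at MPT start. Use the 6-month eligibility window, or 12 months if the claims delivery is confirmed to cover it for every patient.
- **H2:** replace the stated t-test by a cluster-adjusted ANCOVA of the T2 FFbH-R on the T0 FFbH-R. Use T0 because T1 is completed after the 4-week MPT, hence after allocation is disclosed in week 3.
- **Optional:** MPT track as a further covariate, since it follows the severity of the back pain and the initial examination comes before MPT.

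Record the change before outcome data are examined; Statistical analysis already provides for documented, justified deviations. The cost is one degree of freedom for each added covariate, a slightly larger claims extract and revised analysis-plan wording. No further patients or questionnaires are needed. If r proves low, the gain is small and little is lost.

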#### Secondary outcomes

Data for secondary outcome variables will be obtained via questionnaires and claims data. The Markov Chain Monte Carlo approach in SPSS (Version 28) will be used as imputation method to replace missing values.^34–36^ To test the hypothesis H_2_ ‘The intervention increases functional capacity’ and H_4_ ‘The intervention reduces direct and indirect costs’, hypothesis tests (two-sided t-test with a significance level of 0.05) will be performed. The third hypothesis H_3_ ‘The intervention is perceived positively by the participating patients’ will be tested by conducting a pencil–paper questionnaire with the patients. The analyses are carried out using the software programme SPSS (Version 28).

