### Health economic analysis

The health economic analysis will examine the costs, cost savings and cost effectiveness of the intervention. Therefore, intervention costs, expenditures of healthcare utilisation, indirect costs due to incapacity to work and the patient’s health-related quality of life will be assessed. For the calculation of indirect costs, the days of incapacity to work are multiplied by the average hourly wage in Germany, taking into account whether the individuals work full time or part time. The evaluation will be carried out based on claims data. Incremental cost effectiveness will be analysed by considering direct and indirect costs as well as the health-related quality of life of both groups, IG and CG.

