### Statistical analysis

Statistical analysis is performed on the basis of a defined analysis plan. If there are justified deviations from this plan, these will be documented and reported in subsequent publications. Compared with the original plan, the one-sided test with regard to hypothesis H_4_ was changed to a two-sided test, as this seems reasonable.

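### H4 (direct and indirect costs) is tested only with a t-test, which can carry neither covariates nor the cluster term, so the precision available from prior incapacity days the insurer already holds is given up

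*Protocol article*

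**What the plan says.** The article names one test for the cost hypothesis, in Secondary outcomes: "The intervention reduces direct and indirect costs’, hypothesis tests (two-sided t-test with a significance level of 0.05) will be performed". The choice was deliberate. The Statistical analysis section reports that "the one-sided test with regard to hypothesis H_4_ was changed to a two-sided test", so the test was revisited and remained a t-test.

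Indirect cost is built from the primary outcome. Under Health economic analysis, "the days of incapacity to work are multiplied by the average hourly wage in Germany", with allowance for full-time or part-time work. Under Outcome evaluation, "The primary outcome represents the number of days of incapacity to work within 1 year after the end of MPT".

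For H1, the Primary outcome section specifies a cluster-adjusted analysis of covariance with age, gender and comorbidities, and adds an unadjusted two-sided t-test. Prior incapacity days are not among the H1 covariates.

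Table 2 (Study population) requires incapacity of "At least 21 days during the last 6 months" and excludes patients whose cumulative incapacity in that window exceeds 12 weeks. Participant recruitment says that the insurer's staff identify the candidates. The claims-data paragraph under Measurements states that "sociodemographic factors of influence (eg, age, gender and level of education) together with data regarding health-related quality of life will be included in the analysis", without naming a model.

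**The concern.** A two-sample t-test has no place for a covariate or for the monthly cluster. For H4 this sits oddly with the rest of the article. The days that drive indirect cost are analysed for H1 in a model that has both. The Measurements section promises sociodemographic factors in the claims-based analysis. The insurer also holds, before randomisation, an earlier value of the quantity that drives indirect cost.

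The stake is mainly precision. If prior days predict later days, an unadjusted comparison has a wider interval than necessary. A chance difference between arms in prior absence then feeds into the indirect-cost difference with nothing to correct it. The planned baseline comparison of the groups could reveal such a difference, but the H4 test could not use it.

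**Working it through.** **Inputs.** From Sample size calculation: SD 58 days, target difference 15 days, d = 0.3409275, 137 per group before and 147 per group after the design effect, ICC 0.01, mean cluster size (22×16 + 2×8)/24 = 368/24 = 15.33. The article gives no SD, effect size or power for H4, and no correlation rho between pre-MPT and follow-up values. Every rho below is an assumption.

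**The article's own figure.** At two-sided 0.05 and 80% power, the normal approximation gives n = 2(1.960 + 0.842)²/0.3409275² = 135.1, so 136 per group. The noncentral t gives 137, which matches. This figure belongs to H1; none exists for H4.

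**Two SDs.** The printed d implies SD = 15/0.3409275 = 44.0, while the stated SD of 58 gives d = 15/58 = 0.259. That disagreement is a separate matter, so both are carried here.

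**Precision of the unadjusted comparison of days.** Design effect = 1 + (15.33 − 1)×0.01 = 1.143. Effective n per group = 147/1.143 = 128.6. SE = SD×√(2/128.6), which is 5.49 days at SD 44 and 7.23 days at SD 58.

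**Effect of adjustment.** Variance is multiplied by 1 − rho². The interval narrows by 1 − √(1 − rho²). Power ≈ Φ(15/(SE×√(1 − rho²)) − 1.96).

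| Assumed rho | Variance ratio | Interval narrower by | Power, SD 44 | Power, SD 58 |
|---|---|---|---|---|
| 0 (unadjusted) | 1.00 | – | 78.0% | 54.5% |
| 0.1 | 0.99 | 0.5% | 78.4% | 54.9% |
| 0.3 | 0.91 | 4.6% | 81.7% | 58.5% |
| 0.5 | 0.75 | 13.4% | 88.4% | 66.8% |

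Noncentral-t values at rho 0, 0.3 and 0.5 are within 0.3 points (77.7, 81.5, 88.2% and 54.2, 58.2, 66.5%). The figures describe the days. They carry over to indirect cost only so far as the wage multiplier is roughly constant, and they say nothing about direct or total cost.

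**Exposure to chance imbalance.** If the same design effect applies to the baseline value, the standardised baseline difference has SE √(2×1.143/147) = 0.125, so differences up to about 0.24 SD lie within the 95% range. A difference of 0.2 SD or more in either direction (0.2/0.125 = 1.6 SE) arises in roughly 11% of trials. Such an imbalance shifts the unadjusted difference in days by rho×0.2×SD:

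| Assumed rho | SD 44 | SD 58 |
|---|---|---|
| 0.1 | 0.9 days | 1.2 days |
| 0.3 | 2.6 days | 3.5 days |
| 0.5 | 4.4 days | 5.8 days |

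The target is 15 days.

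**Cluster term.** This affects validity rather than efficiency. If the outcome has the planned ICC of 0.01, a t-test that ignores clustering has a true two-sided level of about 2[1 − Φ(1.96/√1.143)] = 0.067. The ICC for cost is not given.

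**The case against.** The strongest reply is that omitting covariates is not an error. Under randomisation, chance imbalance is already part of the sampling error, and the unadjusted difference is unbiased. The gain rests on an assumed rho. At 0.1 it is negligible, and eligibility confines prior incapacity to between 21 days and 12 weeks in 6 months, which may well lower rho. The figures are also borrowed from H1. All of this stands, and it limits the point to precision that could be had at little cost.

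It can also be said that covariate detail for an economic outcome belongs in the analysis plan, to which the article refers. That carries less weight here, because the article names the H4 test rather than leaving it open.

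Three stronger readings are tempting, and the article does not support them:

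- A reader might infer that H1 and the indirect-cost part of H4 could reach different verdicts only because one is adjusted. But the Primary outcome section also runs an unadjusted t-test on the days, so a like-for-like comparison exists.
- A reader might infer that the cost-effectiveness estimate will be unadjusted. No section says so. The t-test is the hypothesis test for H4, and the statement under Measurements is compatible with an adjusted economic model.
- A reader might infer that pre-MPT costs are already in hand. The eligibility criteria establish this for incapacity days and the screening diagnoses. No look-back window is stated for cost items.

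**Conclusion.** The point holds as a matter of efficiency. The only test named for H4 can use neither the pre-MPT incapacity days that the insurer already holds nor the cluster structure. For the missing covariates, the consequence is lost precision and exposure to chance imbalance, not bias on average. The size is a 1%, 9% or 25% reduction in variance at an assumed rho of 0.1, 0.3 or 0.5, for the days component only. The true rho is unknown and may be at the low end, and no figure can be given for direct or total cost. Copying the H1 covariates to H4 would not by itself secure this gain, because H1 does not include prior days either.

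**What to change.** In Secondary outcomes, make the H4 test a cluster-adjusted linear model of cost. Covariates: incapacity days in the 6 months before entry, already held for eligibility; age, gender and comorbidities, as in H1; and level of education, which Measurements already names. Add pre-MPT cost from claims if the extract includes a look-back window. Keep the t-test as a supplementary analysis, as is done for H1.

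The cost is a change of wording, one extra model and possibly a wider claims extract. No additional patient contact is needed.

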## Methods and analysis

### Study design

In order to answer the research questions, outcome, process and health economic analyses will be carried out. Different research methods will be used for this purpose. The comparative population will be formed by randomising the groups of participants. The division into the respective groups (intervention group, IG or control group, CG) will be carried out monthly to ensure that the patients of both groups are not able to exchange information with each other. Patients who start an MPT simultaneously in the Rehabilitation Center each form a cluster. These clusters will be randomised to the IG or CG (see figure 2). The evaluator will inform the Rehabilitation Center monthly via email in the third week of the MPT whether the group is an IG or CG. Up to this point, neither the patient nor the treatment staff will know which group the patient belongs to. The recruitment period will be 24 months.

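### The H2 t-test on functional capacity names no baseline covariate although FFbH-R is collected at T0, which gives up precision at no saving

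*Protocol article*

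**What the plan says.** All references are to the protocol article.

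- **Secondary outcomes.** For H2 and H4, "hypothesis tests (two-sided t-test with a significance level of 0.05) will be performed". No covariate, baseline value or cluster term is named. The section does not say whether the test is on T2 scores or on change from T0. Missing values in secondary outcomes are to be imputed by a Markov chain Monte Carlo method.
- **Primary outcome.** H1 gets an analysis of covariance with cluster adjustment, with age, gender and comorbidities as covariates. This is stated for H1 only.
- **Outcome evaluation.** "It is assumed that the functional capacity in the IG will be significantly (p<0.05) higher than in the CG".
- **Measurements.** The T0 questionnaire is given to both groups before MPT. In it, "standardised survey instruments will be included to assess functional capacity", and the instrument named is FFbH-R. A further questionnaire follows 12 months after the intervention (T2).
- **Study design.** The evaluator tells the rehabilitation centre "in the third week of the MPT whether the group is an IG or CG". Until then neither patients nor treatment staff know the group.

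**The concern.** FFbH-R is measured in the same patient before and after the intervention, and the T0 score is a sound covariate: it precedes MPT and precedes disclosure of the group. A two-sample t-test on T2 scores leaves between-patient variation in T0 inside the error term. A t-test on change from T0 uses the baseline, but with a fixed slope of 1 rather than the slope in the data. Either way the confidence interval is wider than it needs to be.

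There is also a conditional issue. If the groups happen to differ at T0, part of that difference appears in the estimated effect and the named test does not correct for it. The protocol states no power for H2, so precision given up here could leave the hypothesis undecided. The protocol already uses an adjusted model for H1, so the contrast lies within the document itself.

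**Working it through.** **Inputs from the document (Sample size calculation):** 147 subjects per group after allowance for clustering, intraclass correlation 0.01, average cluster size 15.3. All three were set for the primary outcome. They are borrowed here as planning figures, because none is given for FFbH-R.

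**Assumptions:** T0–T2 correlation r of 0.5, 0.6 or 0.7 (not in the document), equal variances at T0 and T2, a linear relation, and H2 assessed at T2.

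**The plan's own figure.** No sample size or power is stated for H2. The stated 137 per group for the primary outcome, before clustering, does follow from the stated d = 0.3409275 (two-sided t-test, 5% level, 80% power): 136.02, rounded up to 137. It does not bear on H2 otherwise.

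**Step 1: precision.** With σ the SD of FFbH-R, the per-patient variance is:
- t-test on T2 scores: σ²
- t-test on change from T0: 2(1 − r)σ²
- ANCOVA on T0: (1 − r²)σ²

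The standard error of ANCOVA is therefore √(1 − r²) times that of the T2-score test, and √((1 + r)/2) times that of the change-score test.

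| r | ANCOVA / T2-score test | SE cut | ANCOVA / change-score test | SE cut |
|---|---|---|---|---|
| 0.5 | √0.75 = 0.866 | 13% | √0.75 = 0.866 | 13% |
| 0.6 | √0.64 = 0.800 | 20% | √0.80 = 0.894 | 11% |
| 0.7 | √0.51 = 0.714 | 29% | √0.85 = 0.922 | 8% |

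These ratios do not depend on the sample size.

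**Step 2: what that means for H2, against a T2-score test.** Ignoring clustering, the difference detectable with 80% power at 147 per group is (1.960 + 0.842) × √(2/147) = 0.327 SD. With adjustment it becomes 0.327 × 0.866 = 0.283, 0.327 × 0.800 = 0.261 and 0.327 × 0.714 = 0.233 SD. An effect of 0.327 SD would then be detected with about 90%, 94% and 97.5% power.

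**Step 3: chance imbalance at T0.**
- Design effect: 1 + (15.3 − 1) × 0.01 = 1.143.
- SD of the chance T0 difference: √(2 × 1.143/147) = 0.125 SD units; 95% limits ±1.96 × 0.125 ≈ ±0.24.
- T2-score test: r times the T0 difference carries over. At r = 0.6 the 95% limit is 0.6 × 0.244 = 0.15 SD, and the median absolute carry-over is about 0.67 × 0.125 × 0.6 = 0.05 SD.
- Change-score test: (r − 1) times the T0 difference carries over. At r = 0.6 the 95% limit is −0.4 × 0.244 = −0.10 SD, that is, in the opposite direction.

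**Step 4: error rate.** A simulation of the T2-score test (20,000 trials for each of r = 0.5 and r = 0.7, 147 per group, no clustering) gave an overall type I error of 5.1%. In the roughly 9% of trials where the T0 difference exceeded 0.2 SD, it was 16% at r = 0.5 and 27% at r = 0.7.

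**The case against.** **The t-test is valid without a baseline term.** This stands. Randomisation keeps the estimate unbiased on average, and chance T0 imbalance is already part of the test's standard error. A reader might infer from the conditional figures in step 4 that H2 is biased or that its 5% level fails for lack of baseline adjustment. The document does not support that: the overall rate from this cause stays near 5%. Lost precision and exposure to imbalance are also largely one effect seen from two sides and should not be counted twice.

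**The test may be on change scores.** This stands as an ambiguity. The wording in Outcome evaluation, a comparison of level between groups, fits T2 scores. The wording of H2 under Aims, that the intervention increases functional capacity, also fits change. That is why both columns are shown. ANCOVA is more precise than either for any r between 0 and 1.

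**The detail may be in the separate analysis plan.** Only in part. The article names the test for H2, so the choice is fixed, not left open. The remark in Measurements that sociodemographic and quality-of-life data will enter the analysis is too general to supply a T0 FFbH-R covariate for H2.

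**Few clusters make imbalance much worse.** A reader might infer this from the 24 monthly clusters. At the protocol's intraclass correlation, clustering raises the SD of the T0 difference only from √(2/147) = 0.117 to 0.125, about 7%.

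**Two wider readings are not supported.** One is that the plan adjusts for T1, measured after disclosure of the group. No section proposes T1 as a baseline or a change from T1. The other is that the EQ-5D comparison has the same fault. The Health economic analysis section states no model for quality of life, and such detail may properly sit in the analysis plan.

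**Conclusion.** The point holds as a gain in precision that is available at no cost. H2 is fixed as a t-test without a baseline covariate although a T0 score, taken before the group is disclosed, is collected. Under an assumed T0–T2 correlation of 0.5 to 0.7, adjustment would reduce the standard error by 13% to 29% against a T2-score test, or by 13% down to 8% against a change-score test. The true size depends on a correlation that the document does not give; at r = 0.3 the cut against a T2-score test would be only about 5% (√0.91 = 0.95).

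The named test is not biased by this omission, and H2 is a secondary outcome, so the point ranks as a recommended improvement. The absence of a cluster term in the same t-test is a separate matter that does affect the error rate; it is not counted in the figures above.

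**What to change.** In Secondary outcomes, replace the t-test for H2 with an ANCOVA or linear mixed model of T2 FFbH-R, with study group and T0 FFbH-R as terms and the same cluster adjustment as is planned for H1. State that the outcome is the T2 score, which also removes the ambiguity between level and change. Include T0 FFbH-R in the imputation already planned, so that a patient with a missing T0 score is kept.

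The cost is wording only: no new data, no extra patients and no change to the 5% two-sided level. The Statistical analysis section already provides for documenting justified deviations and records one change of test, for H4. The change should be made and dated before outcome data are compared by group.
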